**Fig. 6 fig0006:**
[figure not shown]
Avatar visualization with muscle-activity color coding.

**Fig. 7 fig0007:**
[figure not shown]
Experimental protocol and procedures.•**Bar Mode:** Dynamic bar indicators show EMG amplitude for each monitored muscle.•**Graph Mode:** Scrolling waveform graphs display filtered EMG signals in real time.

In the VR condition, feedback will be displayed in a fully immersive virtual environment. In the MR condition, feedback will be overlaid onto the participant’s view of the physical laboratory using the headset’s passthrough cameras.

**Control Group:** Participants will perform the same exercises without augmented feedback and as 3 blocks matching the VR and MR group number of repetitions and rest periods, while wearing the same EMG sensors and motion-capture markers to maintain equivalent instrumentation burden.

During rest intervals, participants will complete brief in-session questionnaires, including the Borg Rating of Perceived Exertion (RPE) scale [18] to assess perceived effort for each exercise.

#### Phase 5: post-exercise assessments (VR and MR groups only)

After completing all exercise trials, participants in the VR and MR groups will complete two post-exercise questionnaires:•**System Usability Scale (SUS)** [19]**:** a 10-item questionnaire assessing perceived usability of the immersive biofeedback system.•**Simulator Sickness Questionnaire (SSQ)** [20]**:** a 16-item questionnaire assessing symptoms of simulator sickness, including nausea, oculomotor discomfort, and disorientation.

The RPE assessment will not be repeated in this phase because it is collected during the rest intervals in Phase 4 for all groups.

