#### Phase 4: experimental exercise trials

Participants will perform the five standardized shoulder exercises in the fixed order established during familiarization for all three visualization modes. Each exercise will include five repetitions using the individually determined working load recorded during Phase 3. Rest intervals of 2–3 min will be provided between exercises to minimize fatigue, and participants may request additional rest if needed. A trial will be stopped if the participant reports pain, dizziness, excessive fatigue, simulator sickness symptoms, skin irritation, or any discomfort that raises safety concerns. Any stopped, repeated, or excluded trial will be documented in the session log.

**VR and MR Groups:** Participants will wear the Meta Quest 3 headset and receive real-time EMG biofeedback through all three visualization modes in a randomized order:•**Avatar Mode:** A 3D avatar mirrors the participant’s movements, as shown in Fig. 6, with deltoid regions colored according to EMG amplitude.

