#### Phase 6: debriefing and equipment removal

All sensors, markers, and headset equipment will be carefully removed. Participants will be debriefed, given an opportunity to ask questions, and monitored for any immediate discomfort. Any adverse events, including muscle soreness, skin irritation, or simulator-sickness symptoms, will be documented.

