#### Secondary outcomes: subjective measures

**Perceived Exertion:** RPE score recorded after each exercise.

**Simulator Sickness:** SSQ total and subscale scores for nausea, oculomotor discomfort, and disorientation in the VR and MR groups.

**System Usability:** SUS score from 0 to 100 in the VR and MR groups, with scores above 68 indicating above-average usability [19].

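### SSQ and SUS are scheduled only after all exercise trials, so a VR or MR participant who ends early for sickness and does not resume has no scheduled score (minor; secondary outcomes)

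*Protocol article*

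**What the plan says.** All places are in the protocol article.

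- **Phase 5 (post-exercise assessments)** fixes the timing of both questionnaires: "After completing all exercise trials, participants in the VR and MR groups will complete two post-exercise questionnaires". These are the SUS and the SSQ.
- **Phase 4 (experimental exercise trials)** gives the stopping rule: "A trial will be stopped if the participant reports pain, dizziness, excessive fatigue, simulator sickness symptoms, skin irritation, or any discomfort that raises safety concerns". What follows a stop is a record: "Any stopped, repeated, or excluded trial will be documented in the session log".
- **Phase 4, rest intervals**, names one instrument: "During rest intervals, participants will complete brief in-session questionnaires, including the Borg Rating of Perceived Exertion (RPE) scale". Neither SSQ nor SUS is named there.
- **Phase 6 (debriefing)** covers symptoms as events: "Any adverse events, including muscle soreness, skin irritation, or simulator-sickness symptoms, will be documented".
- **Secondary outcomes** define the sickness measure as "SSQ total and subscale scores for nausea, oculomotor discomfort, and disorientation in the VR and MR groups" and the usability measure as "SUS score from 0 to 100 in the VR and MR groups, with scores above 68 indicating above-average usability".
- **Exclusion criteria** remove people with a history of motion sickness or marked discomfort in a headset.

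**The concern.** The stated timing ties both questionnaires to finishing every exercise trial. The stopping rule in the phase before names the very symptoms that the SSQ measures. Someone who stops because of those symptoms and cannot go on never reaches the point at which the SSQ is scheduled. The score is then missing because of its own likely value, and the participants lost are the probable high scorers.

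What is at stake is the SSQ summary in each immersive arm and, under further conditions, the contrast between VR and MR, which the Study design section gives as a purpose of the trial. An analysis plan cannot repair this afterwards, because the score would never have been collected. No primary outcome is involved.

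**Working it through.** **Step 1. Follow the schedule as written.** In the VR and MR arms, Phase 4 is five exercises in each of three visualization modes: 5 × 3 = 15 sets. Phase 5 comes after all of them.

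| Course of events | What the article schedules |
|---|---|
| All 15 sets completed | SSQ and SUS in Phase 5 |
| A set is stopped for symptoms; participant recovers, repeats or continues, and finishes | SSQ and SUS in Phase 5, plus a log entry |
| A set is stopped for symptoms; participant does not resume | Log entry and adverse-event record; no SSQ or SUS scheduled |

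Only the third row is a gap. A log entry or adverse-event record gives no SSQ total and no subscale score.

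**Step 2. Size of the effect on mean SSQ.** The article gives no stopping rate, sample size or expected SSQ value, so there is no figure to reproduce. Let C be the mean SSQ of completers, p the share of an arm that permanently ends early, and d the amount by which their SSQ would exceed C.

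- Mean in the whole arm = (1 − p)C + p(C + d) = C + p × d
- Mean among completers = C
- Bias of the completers' mean = −p × d

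The values below are assumptions, not taken from the documents:

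| p | d = 20 | d = 40 | d = 60 |
|---|---|---|---|
| 2% | −0.4 | −0.8 | −1.2 |
| 5% | −1.0 | −2.0 | −3.0 |
| 10% | −2.0 | −4.0 | −6.0 |
| 15% | −3.0 | −6.0 | −9.0 |

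**Step 3. SUS.** If those who end early would score e points lower on SUS, the completers' mean is too high by p × e. With e = 0 the bias is 0 at any p. With p = 15% and e = 20 it is 0.15 × 20 = 3.0 points. Nothing in the documents says that e is above 0.

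**Step 4. VR minus MR.** The distortion of the SSQ difference is −(p_VR × d_VR − p_MR × d_MR).

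- Equal stopping of 5% and a common d of 40: −(2.0 − 2.0) = 0.
- Stopping of 10% in VR and 2% in MR, common d of 40: −(4.0 − 0.8) = −3.2 points, which flatters VR.

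The distortion needs the two products to differ. The documents do not say that they do.

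**Step 5. Would it happen at all?** The chance of at least one such participant in an arm of n is 1 − (1 − p)^n. For an assumed n of 20:

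- p = 2%: 1 − 0.98^20 = 33%
- p = 5%: 1 − 0.95^20 = 64%
- p = 10%: 1 − 0.90^20 = 88%

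**The case against.** The strongest reply is that the Phase 5 wording describes the usual order of a session and is not a rule that withholds the questionnaires. The secondary outcomes are defined for the VR and MR groups without restriction to completers. No sentence sends an early stopper straight to debriefing. Procedures after early termination are often left to a fuller document, the rest-interval questionnaires are introduced by a non-exhaustive list, and Fig. 7, which summarises the procedures, is not shown.

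Part of this stands: the text does not forbid giving the forms to someone who ends early, and staff might do so. But the article fixes a timing condition and does not merely omit a detail. That condition leaves the early stopper without a scheduled score. If the matter is left to discretion, timing will vary between participants.

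Four further limits stand and reduce the point:

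- **The rule stops a trial, not the session.** A reader might infer that every stop for sickness loses an SSQ. It does not: extra rest is available, stopped trials may be repeated, and a participant who finishes is scored.
- **The eligible population is at lower risk.** Participants are healthy, aged 20–30, and have no history of motion sickness, so p may be small.
- **The events are not lost.** A reader might infer that sickness goes unrecorded. The session log and the adverse-event record keep it visible, though not as a score.
- **Direction is settled only for SSQ.** A reader might infer that SUS is also too favourable, or that the VR–MR comparison favours the worse-tolerated mode. The first is plausible but not shown. The second needs unequal permanent stopping or unequal d, which the documents do not establish.

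**Conclusion.** The concern holds for a limited group: VR or MR participants who end exposure for sickness symptoms and do not resume. As the schedule is written, they have no SSQ or SUS, and the SSQ is missing because of what it measures. If there are such participants and their SSQ would exceed that of completers, the mean SSQ among completers is too low by p × d. Under the assumed ranges this is 0.4 to 9.0 points; the true size cannot be found from the documents and may be near the low end. Effects on SUS and on the VR–MR difference are conditional, as set out above. Severity is minor: two secondary outcomes are concerned and no primary outcome is touched.

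**What to change.** Amend the timing sentence in Phase 5 along these lines: *SSQ and SUS are completed at the end of immersive exposure, whether all trials were completed or exposure ended early; the number of visualization blocks completed and the reason for ending are recorded with the scores.* Include these scores in the VR and MR summaries, and report the number of early endings by arm beside them.

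The cost is one sentence. The same two questionnaires go to the same participants, with no extra visit, and the stopping rule is unchanged. The one downside is that SUS from a participant who ends early rests on fewer modes; the recorded block count shows where this applies.

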## Abstract

This paper describes a protocol for a controlled laboratory study designed to evaluate how immersive real-time electromyographic (EMG) biofeedback affects standardized shoulder exercise performance and user experience in healthy adults. Participants aged 20–30 years will be randomly allocated to virtual reality (VR), mixed reality (MR), or a non-immersive control condition. Within the immersive arms, each participant will experience three EMG visualization modes (an anatomically mapped avatar, a dynamic bar display, and a live waveform graph) in randomized order. During five standardized shoulder exercises, bilateral deltoid activity will be recorded using six wireless EMG sensors, while three-dimensional kinematics will be captured with an optical motion-capture system. Outcomes will include joint-angle accuracy, normalized muscle activation, compensatory motion, range of motion, movement speed, task completion time, together with perceived exertion, simulator sickness, and system usability. By integrating synchronized EMG and motion-capture data with immersive feedback delivery, this protocol provides a reproducible framework for comparing VR and MR biofeedback environments and evaluating how visualization mode may influence exercise execution and user experience.•Compares VR, MR, and non-immersive shoulder exercise conditions.•Evaluates avatar, bar, and waveform EMG visualization modes.•Combines EMG, motion capture, and subjective assessments.

Compares VR, MR, and non-immersive shoulder exercise conditions.

Evaluates avatar, bar, and waveform EMG visualization modes.

Combines EMG, motion capture, and subjective assessments.

Specifications table

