A related unresolved issue is how EMG feedback should be visualized. Feedback design can influence attention, cognitive load, motor learning, and dependence on guidance [[10], [11], [12]]. Recent work on muscle-engagement visualization [13] and EMG-based interaction in VR further suggests that the body location, visual representation, and feedback modality can affect performance and workload [14]. However, the comparative effects of anatomically mapped avatar displays, abstract bar indicators, and live waveform graphs during shoulder exercises remain insufficiently understood.

Two methodological gaps, therefore, remain. First, direct comparisons between VR and MR for delivering real-time EMG biofeedback during shoulder exercises are limited. Second, few controlled protocols compare how different EMG visualization modes affect exercise execution and user experience. This protocol addresses these gaps by evaluating real-time EMG biofeedback during standardized shoulder exercises across VR, MR, and non-immersive conditions, while also comparing avatar-, bar-, and graph-based visualization modes. By combining objective kinematic and EMG outcomes with usability, exertion, and simulator-sickness measures, the study provides a structured workflow for quantifying exercise performance and user experience under controlled immersive biofeedback conditions.

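### SUS and SSQ are completed once, after all three visualization modes, so only RPE can show how mode affects user experience, and the SSQ level has no pre-exposure or control value to set it against

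*Protocol article*

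**What the plan says.** - **Aim.** The Abstract presents the protocol as a framework for "evaluating how visualization mode may influence exercise execution and user experience". The Background names as a gap that "few controlled protocols compare how different EMG visualization modes affect exercise execution and user experience" and says the protocol addresses it. The same paragraph lists the user-experience measures: "By combining objective kinematic and EMG outcomes with usability, exertion, and simulator-sickness measures". The section on secondary outcomes contains these three and no others.
- **Exposure.** Under Phase 4, VR and MR participants "receive real-time EMG biofeedback through all three visualization modes in a randomized order", all in one session.
- **Timing of SUS and SSQ.** Under Phase 5: "After completing all exercise trials, participants in the VR and MR groups will complete two post-exercise questionnaires". SUS is described as "assessing perceived usability of the immersive biofeedback system", so the object rated is the system and not a mode.
- **Who completes them.** The Phase 5 heading restricts both forms to the immersive groups, and the SSQ outcome is defined as "SSQ total and subscale scores for nausea, oculomotor discomfort, and disorientation in the VR and MR groups".
- **Before exposure.** Phase 1 has a pre-screening questionnaire and SPADI. Phase 2 is instrumentation and headset fitting. Phase 3 is MVIC testing, familiarization and baseline trials. None of them lists SSQ.
- **RPE.** It is collected in the Phase 4 rest intervals, for each exercise and in all groups.
- **Analysis.** The planned statistical analysis puts a visualization-mode term only in models for outcomes that are repeated across exercises and modes.

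**The concern.** The aim names user experience as something to be compared across avatar, bar and graph. Two of its three measures are taken at a point where every immersive participant has had the same exposure to all three modes. Each score is then one blended rating of the whole session. If, say, the waveform graph were hard to use and the avatar easy, the single SUS score could not show it. A later analysis plan cannot repair this, because the data by mode would not exist.

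There is a second, separate limit on SSQ. By Phase 5 a participant has done 18 maximal contractions, the baseline trials and three loaded exercise blocks. The Phase 4 stopping reasons list dizziness and excessive fatigue next to simulator-sickness symptoms, so the protocol itself expects discomfort of several kinds during the exercise. Without a score before exposure or in controls, the SSQ level may be read as a headset effect when part of it was present on arrival or came from the exercise.

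**Working it through.** The documents give no figure to reproduce on this point. The check is a count of observations, followed by what those observations can identify.

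**1. Observations per immersive participant, by measure**

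| Measure | When taken | Scores per participant | Scores tied to one mode |
|---|---|---|---|
| RPE | after each exercise, Phase 4 | 5 exercises × 3 modes = 15 | 15 |
| SUS | once, Phase 5 | 1 | 0 |
| SSQ | once, Phase 5 | 1 | 0 |

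A within-participant comparison of three modes needs at least one score per mode, so 3. SUS and SSQ have 1 each.

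**2. Is a mode effect on SUS or SSQ estimable?** Give each immersive participant three exposure indicators: avatar, bar, graph. At Phase 5 they are (1, 1, 1) for everyone. They do not vary between participants, so they are collinear with the intercept. The mode contrasts drop out at any sample size. What does vary is the order of the modes. Comparing scores by order, or by the mode seen last, is possible, but it is a between-participant question about sequence and not the mode comparison in the aim.

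**3. What does the SSQ level contain?** Assume for illustration that the post-session mean is a sum of symptoms on arrival (A), symptoms from the exercise (E) and symptoms from the headset condition (H):

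- VR post-session mean = A + E + H(VR)
- MR post-session mean = A + E + H(MR)
- VR − MR = H(VR) − H(MR)

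Randomization makes A equal in expectation, and the exercises and repetitions are the same, so the difference between VR and MR is estimable. The levels are not: two observed means carry four unknowns (A, E, H(VR), H(MR)). A score before exposure would supply A. A post-session score in controls, who do matched blocks without a headset, would supply A + E, leaving H(VR) and H(MR) by subtraction. As planned, pre-exposure SSQ scores = 0 and control SSQ scores = 0.

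**4. Added forms under the fix**

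- Immersive participant: SUS from 1 to 3 (+2 forms × 10 items = 20 items) and SSQ from 1 to 2 (+1 form × 16 items). Total 20 + 16 = 36 items.
- Control participant: SSQ from 0 to 2 (2 × 16 = 32 items); no SUS.
- Time: no completion times are given. Assuming 4 to 8 minutes for the immersive forms, that is 4/120 = 3.3% to 8/120 = 6.7% of a session of about 120 minutes.

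**The case against.** The strongest reply is that the article never promises SUS or SSQ by mode. The Abstract speaks of user experience in general, one of the two Background statements describes the literature, SUS is defined as a rating of the system, and the mode term is confined to repeated outcomes. On that reading SUS and SSQ are whole-session measures and the aim is only worded too broadly. This is fair, and it is why a wording change would resolve the mismatch. It does not remove it: the Background says the protocol fills the mode gap for user experience, and the same paragraph lists usability and sickness among its measures.

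A reader might go further and infer that the user-experience-by-mode aim cannot be answered at all. The documents do not support that. RPE is a listed subjective outcome and is collected within each mode block, so the aim can be met for exertion. The primary outcomes also keep their mode comparison.

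A reader might also infer that SUS and SSQ are of no comparative use. That is wrong too. Allocation to VR or MR is randomized, so their post-session comparison is valid without a baseline; a pre-exposure SSQ would add precision, not validity. No stated analysis uses SSQ change or SSQ against control, so that part of the fix is an improvement and not the correction of an error.

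Three further defences do not change the result:

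- The wording on in-session questionnaires leaves room for forms besides RPE, but Phase 5 expressly places SUS and SSQ after all trials.
- The motion-sickness exclusion and the adverse-event record do not give a same-day baseline score.
- The Limitations mention carryover between modes, but not that usability and sickness go unmeasured by mode.

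**Conclusion.** The concern holds in a limited form. SUS and SSQ offer no mode contrast, at any sample size, so two of the three user-experience measures cannot speak to an aim that the Abstract and Background state. RPE can. The VR-versus-MR comparison of both questionnaires stands. The SSQ level in either immersive group cannot be attributed to the headset.

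The first conclusion rests only on the stated timing and exposure. The second rests on no SSQ being given in Phases 1 to 3 or to controls, as the article describes; the additive split above is an illustration. The outcomes affected are secondary. The point is still worth acting on, because it uses instruments already in the study, costs little and cannot be repaired once data are collected. The pilot reported is a one-participant workflow check made before full data collection, so on the article's own account the schedule can still be changed.

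**What to change.** 1. Give SUS at the end of each visualization block, worded for the mode just used. Analyse it with group, mode and block order.
2. Give SSQ before headset fitting in Phase 2 (at the same stage for controls) and again after Phase 4, in all three groups. Analyse the post score adjusted for the pre score.
3. State that SSQ is a whole-session measure, and take sickness out of the mode-comparison aim in any case: pre and post scores still give no mode contrast.
4. If per-block SUS is not adopted, limit the user-experience-by-mode aim to RPE and describe SUS as a whole-session VR-versus-MR measure.

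The cost is two more SUS forms and one more SSQ form per immersive participant, two SSQ forms per control, and changes to the procedure text. No new instrument is needed. The added minutes are an assumption. The article states 2–3 minute rests between exercises but no separate rest between blocks, so room for a block-end SUS has to be confirmed. Ratings may also carry over from one block to the next; the varied mode order and the block-order term reduce this but do not remove it.

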#### Phase 6: debriefing and equipment removal

All sensors, markers, and headset equipment will be carefully removed. Participants will be debriefed, given an opportunity to ask questions, and monitored for any immediate discomfort. Any adverse events, including muscle soreness, skin irritation, or simulator-sickness symptoms, will be documented.

### Outcome measures

#### Primary outcomes: objective measures

**Joint Angle Accuracy:** Deviation of measured shoulder joint angles, including flexion, abduction, and rotation, from the prescribed target range for each exercise. Lower deviation indicates greater movement accuracy.

**Muscle Activation Patterns:** EMG amplitude normalized to MVIC for each monitored deltoid muscle. Metrics include mean activation, peak activation, and activation timing.

